## **7.6 Criteria for stopping treatment**

Volunteers/participants may discontinue further immunisations at any time if they wish to do so, for any reason. The date of discontinuation and reason for doing so will be recorded in a case record form.

The clinical investigator may decide that it is not in the best interests of the volunteer/participant to proceed to the next immunization if the investigator deems that

continuing might compromise participant wellbeing or interfere with the achievement of the trial's objectives. Participants who are discontinued due to a clinical or social adverse event (AE) will be followed up until the event has stabilised. The event should be reported as described in **sections 8.2.1 and 8.2.2**.

The following are examples of circumstances in which the clinical investigator would discontinue the injection schedule in a participant:

1. HIV infection
2. Pregnancy
3. Type 1-hypersensitivity associated with immunization.
4. Any medical condition that can recur/deteriorate with further immunizations.
5. Need for systemic glucocorticoids or immunomodulators other than NSAIDs for any reason.
6. The Sponsor, vaccine provider or principal investigator decides to stop or cancel the study.
7. The ethical or regulatory authorities decide that the study be stopped.

Trial volunteers who are discontinued from additional study injections will continue to be followed according to the schedule to further evaluate safety and monitor adverse events, unless they wish to withdraw from the study entirely, in which case they are free to do so. The frequency of visits and laboratory investigations may be reduced on consultation with the Principal Investigator and TMG. Participants who have received any immunisations should be asked to undergo the procedures scheduled for the primary endpoint visit as a minimum. They will also continue to be covered by the medical insurance until the end of the study period.

No serious adverse reactions are expected for these immunogens, and over 200 subjects have been exposed. However, this is the first time the DNA is being administered with electroporation, and the first time MVA-CMDR and CN54rgp140/GLA-AF will be administered at the same timepoint. In the event of a suspected serious adverse reaction this will be unexpected and will therefore be classified as a SUSAR (Suspected Unexpected Serious Adverse Reaction). Such events must be reported to the regulatory authority within 24 hours if fatal or an immediate threat to life (see **section 8** for further details). The Chief Investigator will inform the Sponsor's Medical Expert and organise the expert multi-disciplinary review within 3 working days, and further immunisations in all participants will be suspended pending this review.

A component of the expert review will be to consider whether or not further immunisations for that group, or for all groups should be held whilst further investigation into the event is undertaken, and whether or not to call an unscheduled meeting of the Data Safety Monitoring Board (DSMB) to review the accumulated safety data for one or all treatment groups.

The DSMB will be asked to make a recommendation with respect to further immunisations in the trial. This recommendation will be shared with the local and national ethics committees and regulatory authorities.

The decision to stop further immunisations rests with the Sponsor, and the Sponsor reserves the right to stop the whole trial at any time, which could include following a recommendation from the DSMB, the local or national ethics committees, or the national regulatory authorities.

## **7.7 Procedures at the end of the trial**

The trial will be closed when all participants have made their final follow-up visit (Visit 17 or optionally visit 18), the data entered into the database and the database locked. There will be a final monitoring/closeout visit to the clinical sites between the last visit and the database lock.

## **7.8 Sub study: participants and community related perceptions**

### **7.8.1 Rational and Background of the sub study**

Recruitment and acceptance for HIV vaccine trials are largely dependent on the knowledge, perceptions and attitude towards HIV vaccine development within the volunteers' communities. Following experiences of HIV Vaccine trials in Mbeya (RV 172 and TaMoVac I), Dar es Salaam (HIVIS-03 and TaMoVac I) and Maputo (TaMoVac I); members of the communities have misconceptions about HIV Vaccine trials thereby posing challenges towards recruitment and retention of trial participants. As these trials aim to eventually lead to efficacy studies being conducted within the communities, assessing community knowledge, perceptions and recommendations for strategies that will effectively engage volunteers in HIV Vaccine trials will be helpful in establishing trustful relations with trial researchers, minimizing misconceptions and consequently improving recruitment and retention of trial volunteers. The community awareness sub study will be the topic of the thesis of [name] from the NIMR-Mbeya Medical Research Center (MMRC) within her Master of International Public studies at the University of Liverpool, UK throughout TaMoVac II. The study will therefore mainly focus on Mbeya but the interpretation is expected to involve collaboration with the social science sections of the TaMoVac II Dar es Salaam and Maputo group. Any involvement of volunteers and researchers in Mozambique will be preceded by the respective ethics approval by the National Health Bioethics Committee of Mozambique.

### **7.8.2 Sub study objectives**

1. To assess community awareness and perceptions regarding ongoing HIV Vaccine trials
2. To explore study participants' perceptions about HIV Vaccine trials
3. To inform researchers with community driven strategies that would effectively engage communities in HIV Vaccine trials and establish trust towards trial researchers.

### **7.8.3 Sub study population**

Communities residing in areas where former HIV Vaccine trial recruitment has taken place as well as those who were not addressed by recruitment strategies but reside within the trial catchment area. In addition, potential study participants attending briefing sessions for TaMoVac II will also be included in the study sample.

### **7.8.4 Sub study methods**

#### **Data collection**

Focus Group Discussions and questionnaires will be used to generate information regarding knowledge as well as perceptions of both communities and potential study participants towards HIV Vaccine trials. Such methods will also explore strategies recommended by communities and potential study participants to effectively engage them in HIV Vaccine trials as well as those that help to build up and maintain trust towards HIV Vaccine trial researchers. Data from focus group discussions will be recorded using tape recorders.

#### **7.8.5 Ethical consideration and confidentiality**

All interview and focus group discussion related data will be used coded to maintain confidentiality of interviewees. No personal identifiers will be used throughout data collection. Participants will be requested to withhold fellow participant responses, comments and identity within the group discussions.

Structured questionnaires and procedures for recruiting volunteers will be submitted to the local IRB at Mbeya, MUHAS and the National Health Bioethics Committee of Mozambique (as applicable) as amendments for approval prior to sub study related activities.

## 8 SAFETY REPORTING

Tanzanian and Mozambican clinical trials regulations require that both investigators and sponsors follow specific procedures when notifying and reporting adverse events/reactions in clinical trials. These procedures are described in this section of the protocol. **Section 8.1** lists the definitions; **section 8.2** describes details of the responsibilities of the institutions/investigators.

### 8.1 Definitions and Classification

An **Adverse Event (AE)** is any untoward medical occurrence in a patient or clinical investigation subject administered a pharmaceutical product and which does not necessarily have a causal relationship with this treatment. An AE can therefore be any unfavourable and unintended sign (including abnormal laboratory finding), symptom or disease temporally associated with the use of a medicinal (investigational) product, whether or not related to the medicinal (investigational) product (ICH E6). An adverse event in this study is any adverse experience occurring during the course of the study starting after enrolment.

An **Adverse Reaction** is any untoward and unintended response in a subject to an investigational medicinal product which is related to any dose administered to that subject. 'Related' means possibly, probably or definitely as defined below.

An **Unexpected Adverse Reaction** is defined as an adverse reaction of which the nature or severity is not consistent with the information about the medicinal product in question set out in the Investigator's Brochure. Any AR that is considered possibly, probably or definitely related to study product according to the classification below meets the criteria for "unexpected".

A **Serious Adverse Event (SAE)** or Serious Adverse Reaction (SAR) or Suspected Unexpected Serious Adverse Reaction (SUSAR) is any adverse event or adverse reaction if it results in the following (ICH E6 and E2A):

1. Death,
2. A threat to life at the time of the event
3. Requires in-patient hospitalization or prolongs existing hospitalization (hospitalization for an elective treatment is not considered a Serious Adverse Event)
4. Results in persistent or significant disability or incapacity
5. Is a congenital anomaly
6. Is any other important medical condition\*

\*Examples of conditions regarded as "any other important medical condition" include allergic bronchospasm requiring intensive emergency treatment, seizures or blood dyscrasias, which did not result in hospitalization or development of drug dependency.

**Note:** Grade 4 lab abnormalities are not serious adverse events, unless they are related to a clinical event matching the SAE definition. Any grade 3 and 4 lab event needs to be confirmed within 48 hours.

**Note:** Interventions or hospitalization for elective treatment, e.g. cosmetic surgery, tubal ligation or sterilization, hospitalization due to labour are not considered as adverse events unless complications related to the elective treatment occurs.

***Any HIV infection occurring throughout the study period will not be defined as a Serious Adverse Event but needs to be reported within 2 working days of awareness (see section 8.2)***

***Any Social Harm related to study participation or vaccination will be defined and graded as an Adverse Event (e.g. denial of health and life insurance, employment, immigration and marriage relationships).***

### **8.1.1 Adverse Event Grading and Relationship**

The severity of adverse events will be determined by the investigator, based on the DAIDS Table for Clinical and Lab Criteria for Definitions (**see Appendix 8**) or if the event is not listed the event will be graded following these guidelines:

- Mild (Grade 1): Transient or mild symptoms; no limitation in activity; no intervention required. Symptoms causing no or minimal interference with usual social and functional activities
- Moderate (Grade 2): Symptoms causing greater than minimal interference with usual social and functional activities. No or minimal intervention required. It is uncomfortable or an embarrassment.
- Severe (Grade 3): Symptoms causing inability to perform usual social and functional activities. Medical intervention often required.
- Potentially life-threatening (Grade 4): Symptoms causing inability to perform basic self-care functions OR Medical or operative intervention indicated to prevent permanent impairment, persistent disability, or death.

The relationship of adverse events to study product will be classified as:

|                       |                                                                                                                                                                                                                     |
|-----------------------|---------------------------------------------------------------------------------------------------------------------------------------------------------------------------------------------------------------------|
| Unrelated      | adverse events that can be clearly explained by extraneous causes and for which there is no plausible association with study product, or adverse events for which there is no temporal relationship                 |
| Unlikely to be | adverse events that may be temporally linked, but which are much more likely to be due to other causes than study product and which do not get worse with continuing use of product                                 |
| Possibly       | adverse events that could equally well be explained by study product or other causes, which are usually temporally linked and may improve when not using study product but do not reappear when using study product |
| Probably       | adverse events that are temporally linked and for which the study product is more likely to be the explanation than other causes, which may improve when not using study product                                    |
| Definitely     | adverse events that are temporally linked and for which the study product is the most likely explanation, which disappear or decrease when not using study product and reappear when using study product            |

A severe adverse event is any **graded 3 or 4** by the criteria in the DAIDS Toxicity Table (Appendix 8). Some, but not all grade 3 and 4 adverse events will be "serious" by ICH GCP criteria above (section 8.1).

## 8.2 Adverse events that require expedited reporting by the centres

Adverse and serious adverse events will be recorded on the Adverse Events case record form. Any severe clinical adverse event (grade 3 or 4), any serious adverse reaction or unexpected adverse reaction should be reported within 24 hours after site awareness to the Study Monitors, Sponsor, TMG, WRAIR and DSMB, and on to the Tanzanian and Mozambican ethics committees and regulatory authorities according to each authority's requirements. Any grade 3 or 4 fever must persist for 48 hours to meet the definition of severe fever..

Although post immunisation solicited local and systemic adverse events are documented separately from AEs, they are reported as above if they meet SAE or study pause rule definitions. Therefore the PI or designee must review both Vaccine/Reaction and Adverse Event CRFs to ensure prompt and complete identification of all the events described above that require expedited reporting.

**Expedited reporting** within 24 hours of the site awareness of the event is warranted for:

1. A clinical or social harm event resulting in a decision to discontinue the vaccination schedule
2. Administration of the incorrect vaccine or placebo
3. Any serious adverse events
4. Pregnancy
5. HIV infection

## 9 STATISTICAL CONSIDERATIONS

By the end of this study up to 198 study participants will have been exposed to DNA, MVA with and without CN54rgp140 adjuvanted with GLA-AF or saline. Participants will be randomized to vaccine or placebo in a 10:1 ratio.

### 9.1 Method of randomisation

Participants will be block-randomised centrally using a computer-generated algorithm.

### 9.2 Outcome measures

#### 9.2.1 Primary outcomes

##### 9.2.1.1 Immunogenicity

- The primary **immunogenicity** endpoint will be determined from the following results:
  - a positive response in the HIV peptide-specific  $\gamma$ -IFN Elispot assay using freshly isolated PBMCs collected 2 weeks after the final vaccination. A positive result will be defined as the numbers of spot-forming cells (SFC) more than four times the background (RPMI medium only) and > 55 SFC per million PBMC (Merck definition)
  - the magnitude of the  $\gamma$ -IFN Elispot assay response which will be restricted to those samples which have been defined as positive, as measured by the SFC 2 weeks after the final vaccination
  - the endpoint titre or concentration of systemic IgG CN54rgp140 specific antibodies measured 2 and/or 4 weeks after the final vaccination
  - the presence of neutralising antibodies to tier 1 and tier 2 viruses and the titre when these are present

##### 9.2.1.2 Safety

The primary **safety** endpoint is a grade 3 or above local or systemic clinical and laboratory solicited adverse event (see **section 7, Table 2**) or any grade of adverse event that results in a clinical decision to discontinue further immunisations.

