### 1.1.4 Outcome measures

#### Safety

- Grade 3 or above local solicited adverse event (**Table 2**)
- Grade 3 or above systemic clinical and laboratory solicited adverse event (**Table 2**)
- Any grade of adverse event that results in a clinical decision to discontinue further immunisations
- Any grade of adverse event that occurs in a participant that has received at least one immunisation

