### 2.3.1 Hypotheses to be explored

Preclinical studies indicate that ID electroporation increases the efficiency of DNA priming. Although intramuscular electroporation is proven in humans effective it is hampered by discomfort. ID electroporation appears to be well tolerated and may thus be suitable for use in large trials in developing countries. Our first hypothesis is that electroporation will increase the efficiency of DNA priming in terms of immune responses and will lead to a dose sparing DNA vaccine regimen. Furthermore increased DNA vaccine concentration will reduce the number of shots necessary to deliver the full dose with the hypothesis to induce comparable immune responses as with lower DNA vaccine concentrations. Our second hypothesis is that simultaneous administration of MVA with CN54rgp140/GLA-AF after priming with DNA will result in significantly enhanced immune responses without compromising safety relative to MVA alone.

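### The stopping limb of the primary safety endpoint counts only clinical decisions, so a participant who refuses further doses over an event that is not a solicited grade 3+ event is a non-event

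*Protocol*

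**What the plan says.** Protocol section 9.2.1.2 defines the primary safety endpoint with two limbs. The severity limb is "a grade 3 or above local or systemic clinical and laboratory solicited adverse event". The stopping limb is "any grade of adverse event that results in a clinical decision to discontinue further immunisations". The summary, section 1.1.4, uses the same words: "Any grade of adverse event that results in a clinical decision to discontinue further immunisations".

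Section 7.6 describes two ways out of the schedule. One belongs to the participant: "Volunteers/participants may discontinue further immunisations at any time if they wish to do so, for any reason". The other belongs to the clinician: "The clinical investigator may decide that it is not in the best interests of the volunteer/participant to proceed to the next immunization". On the participant's route it adds: "The date of discontinuation and reason for doing so will be recorded in a case record form".

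Section 9.5.1 puts everyone randomised and given at least one immunisation into the ITT population. Section 9.5.3 analyses the primary safety endpoint as a proportion with a confidence interval and compares groups by Fisher's exact test. Section 9.2.2.2 has a secondary outcome of any adverse event of any grade after at least one immunisation.

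**The concern.** The any-grade stopping limb is the only part of the primary safety endpoint that can register intolerability other than as a solicited event of grade 3 or above. Since 7.6 separates the participant's choice from the investigator's decision, the limb registers one route and leaves out the other. A volunteer who has a grade 2 reaction and declines the next dose has stopped because of an adverse event, yet stays in the denominator as a non-event. That volunteer also receives fewer later doses at which a solicited grade 3 event could occur.

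Both primary objectives (1.1.3) compare safety between regimens, and the second hypothesis (2.3.1) is a better response with no loss of safety. A missing component that differs by arm would pull such a comparison towards no difference, or towards the arm that people tolerate less well.

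Labelling adds to this. Section 1.1.1 says that clinical staff know who is allocated to electroporation and who receives one or two injections. When a volunteer and a clinician agree after a reaction not to go on, staff who know the group settle whether that is recorded as a clinical decision or as the participant's wish, and under the present wording the label decides endpoint status.

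**Working it through.** **1. Which participants are missed**

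| Event before stopping | Who decides to stop | Primary safety endpoint? | Reason |
|---|---|---|---|
| Solicited, grade 3 or above | Investigator or participant | Yes | Severity limb |
| Solicited, grade 1–2 | Investigator | Yes | Stopping limb |
| Unsolicited, any grade | Investigator | Yes | Stopping limb |
| Solicited, grade 1–2 | Participant | **No** | Neither limb |
| Unsolicited, any grade | Participant | **No** | Neither limb |

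The gap is the last two rows. Those events still enter the secondary any-grade outcome, but that outcome does not separate events that ended immunisation from events that did not.

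**2. Is there a figure in the plan to reproduce?**

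Not for safety. The power tables in 9.3 concern immune responses. They reproduce with a two-sided pooled-variance test at alpha 0.025 (n=60) and 0.05 (n=90): for 40% to 70% I get 86.7% and 98.6% against the stated 86 and 98. This confirms the group sizes and alphas used below. The protocol gives no safety event rate and no refusal rate, so everything from here on is illustration.

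**3. Size if refusals occur in one group only**

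Inputs: 60 per DNA group (9.3) and Fisher's exact test (9.5.3). Assumed: 3 of 60 counted events in each group, plus *r* event-driven refusals in one group, none with a solicited grade 3+ event. Omitted difference = *r*/60.

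| *r* | Omitted difference | As written | With refusals counted | Fisher p, refusals counted |
|---|---|---|---|---|
| 2 | 3.3 points | 3/60 v 3/60, p=1.00 | 5/60 v 3/60 | 0.72 |
| 4 | 6.7 points | same | 7/60 v 3/60 | 0.32 |
| 6 | 10.0 points | same | 9/60 v 3/60 | 0.13 |
| 9 | 15.0 points | same | 12/60 v 3/60 | 0.025 |

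The base rate matters little to the pattern. From 1/60, eight refusals give 9/60 v 1/60, p=0.017. From 6/60, twelve give 18/60 v 6/60, p=0.011.

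**4. Size if refusals are balanced**

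With *r*=4 in both groups the true table is 7/60 v 7/60 and the recorded one is 3/60 v 3/60. Each difference is zero and each p is 1.00. What is wrong is the level: 5.0% is reported instead of 11.7%.

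**5. Power depends on how much of an excess is stopping**

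Exact Fisher power, 60 per group, two-sided 0.025 (assuming that the alpha for the first randomisation also serves the safety comparison), assumed 3% in control. If a fraction *s* of the excess is event-related stopping and a fraction *f* of those stops is participant-led, the counted rate is 3% + excess × (1 − *s·f*).

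| Total excess | *s* | *f*=0 | *f*=0.25 | *f*=0.50 |
|---|---|---|---|---|
| 15 points | 1 | 0.60 | 0.36 | 0.14 |
| 15 points | 0.25 | 0.60 | 0.55 | 0.48 |
| 10 points | 1 | 0.28 | 0.14 | 0.05 |

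The large losses need *s*=1, that is, an excess made up wholly of stops. With a total excess of 5 points, power is about 0.05 even when every stop counts.

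**6. Fewer later doses**

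With an assumed solicited grade 3+ risk of 2% per immunisation visit, independent across visits, five visits give 1 − 0.98⁵ = 9.6% and one visit gives 2%. Someone who refuses after the first visit is counted as a non-event with most of that risk removed.

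**The case against.** **The gap is narrower than all reaction-driven refusals.** A reader might infer that anyone who refuses after a reaction is scored event-free. Section 9.2.1.2 does not support that: a solicited event of grade 3 or above counts under the severity limb whoever stops. This stands.

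**The direction is conditional.** A reader might conclude that the definition favours the less tolerable arm in any case. It does so only if these refusals are more frequent in that arm, and the protocol gives no rates. This stands.

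**The documents do not predict a large excess.** The discomfort remark in 2.3.1, "Although intramuscular electroporation is proven in humans effective it is hampered by discomfort", concerns the intramuscular route. This trial uses the intradermal route, which the same section describes as apparently well tolerated. Sections 2.1.8.2 and 2.4.6 agree, and section 2.3 reports mostly mild reactions to the protein boost in 40 participants. This stands: the remark cannot support an expected refusal rate here.

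**Section 8.2 is not a contradiction.** Its expedited-reporting item, "A clinical or social harm event resulting in a decision to discontinue the vaccination schedule", does not require the decision to be clinical. A reporting trigger may properly be wider than an endpoint, so the difference shows only that the protocol has broader wording available.

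**Refusals are visible elsewhere.** Reasons go on a CRF (7.6), discontinuations are reported to the sponsor and DSMB (6.5), and tolerability is measured by diary and interview (7.5.5). This is true, and it limits the harm, but none of it enters the primary comparison.

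**Requiring a clinical decision is a defensible choice for specificity.** Participants experience electroporation and a second injection directly, so their stated reasons are subjective and not masked. This has weight. It is why the result on clinical decisions alone should stay visible. It does not justify leaving the other route out, because the clinician's label is also given with knowledge of the group.

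**Conclusion.** The point holds in a limited form. As written, a participant who refuses further doses because of an event that is not a solicited grade 3+ event is a non-event in the primary safety comparison. Bias between arms follows only if such refusals differ by arm; if they are balanced, mainly the event level is understated. The size cannot be fixed from the protocol. The 3.3 to 15 points above come from assuming two to nine refusals in one group of 60, and the power losses are equally illustrative: the steepest assume that a 15-point excess consists entirely of stopping. This is a worthwhile, cheap repair of an endpoint definition. It does not show that the safety comparison is invalid. It is not merely a matter for the analysis plan, because the protocol itself fixes the definition and 9.5.3 ties the primary safety analysis to it.

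**What to change.** In 9.2.1.2 and 1.1.4, define the stopping limb as an adverse event of any grade that results in discontinuation of further immunisations, whether the investigator decides or the participant decides and the recorded reason is an adverse event. Take the reason from the CRF that 7.6 already requires. Have participant-stated reasons classified as event-related or not, blind to group where possible, before the main analysis. Tabulate the two routes separately by group, so that the result on clinical decisions alone remains as a sensitivity analysis.

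The cost is one sentence in two sections and a matching entry in the analysis plan. No new data are needed and no rule on who stops immunisation changes. The downside is that some stated reasons will be hard to classify and are given by people who know what they received; the separate table lets a reader judge how much that matters.
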